## Methods

The study is designed as a randomized, open-label, single-center, crossover study evaluating the effectiveness of combined therapy with rosuvastatin and ezetimibe for hypercholesterolemia. The study is conducted with full respect to regulations established in the Declaration of Helsinki. The eligibility criteria for enrollment into the study include adult patients with hypercholesterolemia defined according to the European guidelines [2] and ineffectiveness of statin monotherapy in the treatment of hypercholesterolemia after at least 6 weeks. All study participants will have been on statin therapy due to secondary prevention indications. Furthermore, they are eligible for the study when, despite statin monotherapy, the LDL-C concentration is higher than 70 mg/dL. Key exclusion criteria include the following: active liver disease; unexplained persistent increase in serum transaminase levels, including more than three times the upper limit of normal activity of one of them; severe renal impairment (creatinine clearance <30 mL/min); myopathy; concomitant treatment with cyclosporine and gemfibrozil; pregnancy or lactation; women of childbearing age not using effective methods of contraception; symptoms of muscle damage after using statins or fibrates in the past; activity of creatine kinase of more than five times the upper limit of normal.

The study is provided by the Department of Cardiology, Antoni Jurasz University Hospital No. 1 in Bydgoszcz, Poland.

After the enrollment, all participants are randomized into one of two arms receiving rosuvastatin and ezetimibe. The study drug (rosuvastatin with ezetimibe) is given: (1) in the morning (8:00 am) for 6 weeks and then in the evening for the next 6 weeks in the first arm; (2) in the evening (8:00 pm) for the first 6 weeks and then in the morning for the following 6 weeks in the second arm. In order to encourage adherence to the treatment, all patients will receive the study drug free of charge over the entire observational period. We plan to enroll 200 patients with ineffectively treated hypercholesterolemia. The scheme of the study and detailed plan of the study are presented in Figs. 1 and 2, respectively. The Standard Protocol Items: Recommendations for Interventional Trials (SPIRIT) checklist is provided as Additional file 1.

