### Endpoints

The primary outcome of the study is change in LDL cholesterol (LDL-C) at 6 (0 vs 6) and 12 (0 vs 12) weeks, as well as between the 6^th^ and 12th weeks, of study drug treatment (combination of ezetimibe and rosuvastatin), depending on the time of day of study drug administration.

The secondary endpoints include:Change in total cholesterol, high-density lipoprotein cholesterol (HDL-C), triglycerides (TGs), apolipoprotein B (ApoB), apoliprotein AI (Apo AI), non-HDL-cholesterol, small, dense-LDL-cholesterol (sd-LDL-cholesterol), lipoprotein(a) at 6 (0 vs 6) and 12 (0 vs 12) weeks, as well as between the 6th and 12th weeks of study drug treatment (combination of ezetimibe and rosuvastatin), depending on the time of day of study drug administrationAssessment of glucose metabolism parameters: glucose, glycated hemoglobin (HbA1c) at baseline and at 6 (0 vs 6) and 12 (0 vs 12) weeks, as well as between the 6th and 12th weeks of treatment with study drugAssessment of high-sensitivity C-reactive protein (hsCRP) at baseline and at 6 (0 vs 6) and 12 (0 vs 12) weeks, as well as between the 6th and 12th weeks of treatment with study drugAssessment of aspartate aminotransferase (AST), alanine aminotransferase (ALT), gamma-glutamyl transferase (GGT), and creatine kinase (CK) at baseline and at 6 (0 vs 6) and 12 (0 vs 12) weeks, as well as between the 6th and 12th weeks of treatment with study drugAssessment of plasma fluorescence using stationary and time-resolved fluorescence spectroscopy at baseline, at 6 (0 vs 6) and 12 (0 vs 12) weeks, as well as between the 6th and 12th weeks of treatment with study drug

Apart from the analysis in the whole population, the above-mentioned endpoints will be analyzed in subgroups depending on age, sex, and presence of other comorbidities.

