### The statistical analysis

Since there is no reference study examining the effectiveness of combined treatment of hypercholesterolemia with rosuvastatin and ezetimibe according to timing of drug administration, we decided to perform an internal pilot study of 20 patients to estimate the final sample size. The means and standard deviations of reduction in LDL-C were 53.25 ± 31.49 mg/dL and 57.71 ± 30.35 mg/dL during morning and evening administration, respectively. The correlation coefficient between total cholesterol reduction during morning and evening drug administration was 0.901. Based on these results and assuming a two-sided alpha value of 0.005, we calculated using the *t* test for dependent variables that enrollment of 157 patients would provide a 98% power to demonstrate a significant difference in total cholesterol level. To compensate for potential withdrawal of consent or loss of study participants due to other reasons, we plan to enroll 200 patients.

The statistical analysis will be carried out using the Statistica 12.0 package (StatSoft, Tulsa, OK, USA). Normal distribution of quantitative variables will be assessed with the Shapiro-Wilk test. Depending on the results of the Shapiro-Wilk test parametric, the Student *t* tests, the one-way analysis of variance (ANOVA) or a non-parametric test (the Mann-Whitney *U* test, Wilcoxon’s signed rank test, or the Kruskal-Wallis ANOVA, multiple comparison test) will be used. The χ^2^ test, the χ^2^ with the Yates correction, or Fisher’s exact test will be used for qualitative variables depending on subgroup size. To assess factors influencing plasma fluorescence parameters, correlation analysis and multiple regression analysis will be conducted. Two-sided differences will be considered significant at *p* < 0.05.

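### The crossover is sized and analysed without a period term, and one-way ANOVA and Kruskal-Wallis do not suit repeated measurements in the same patients

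*Protocol article*

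**What the plan says.** Under Methods the article describes the trial as follows: "The study is designed as a randomized, open-label, single-center, crossover study". One arm takes the drug "in the morning (8:00 am) for 6 weeks and then in the evening for the next 6 weeks in the first arm"; the other takes it in the reverse order. Under Endpoints the primary outcome is "change in LDL cholesterol (LDL-C) at 6 (0 vs 6) and 12 (0 vs 12) weeks, as well as between the" two follow-up visits, by time of day of administration. Each patient therefore contributes LDL-C at weeks 0, 6 and 12 and is observed under both times of day.

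The statistical analysis section bases the sample size on a t test for dependent variables. The pilot LDL-C reductions are given as "53.25 ± 31.49 mg/dL and 57.71 ± 30.35 mg/dL during morning and evening administration", and the correlation sentence reads "The correlation coefficient between total cholesterol reduction during morning and evening drug administration was 0.901".

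For the analysis, a Shapiro-Wilk result decides which family of tests applies. The list opens with Student's test and continues: "the one-way analysis of variance (ANOVA) or a non-parametric test (the Mann-Whitney". It closes with the paired rank method and the k-group rank method: "signed rank test, or the Kruskal-Wallis ANOVA, multiple comparison test) will be used". Chi-square, Yates-corrected chi-square or Fisher tests "will be used for qualitative variables depending on subgroup size".

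The section ties no test to the morning-evening comparison. It names no period or sequence term, no repeated-measures or Friedman analysis and no mixed model. Regression is mentioned only for plasma fluorescence.

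**The concern.** In a two-period crossover, time of day is compared within patients, but it is mixed with whatever changes between week 6 and week 12. Randomising the order balances that change across the two times of day; it does not remove it from the analysis. A paired test that ignores period has two weaknesses:

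- With equal sequences, the period change enters the estimated standard error, so the test becomes conservative and loses power.
- With unequal numbers of completers, part of the period change also enters the morning-evening estimate as bias.

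Both conditions are plausible. The Background section itself says that adherence falls as treatment continues, and the enrolment target allows for losing 43 of 200 patients.

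One-way ANOVA and Kruskal-Wallis have a different problem. They assume independent groups, whereas weeks 0, 6 and 12 are three measurements on the same people.

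**Working it through.** **Inputs from The statistical analysis section.** Morning 53.25 (SD 31.49) and evening 57.71 (SD 30.35) mg/dL; correlation 0.901; 157 pairs. The correlation is labelled as total cholesterol but is used here with the LDL-C SDs, since no other is given.

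**Basic quantities**

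- Difference: 57.71 − 53.25 = 4.46 mg/dL.
- SD of the paired difference: √(31.49² + 30.35² − 2 × 0.901 × 31.49 × 30.35) = √(991.62 + 921.12 − 1722.21) = √190.53 = 13.80.
- Standard error: 13.80/√157 = 1.10.

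**The plan's own figure.** A paired t test with 157 patients has 98.0% power at two-sided alpha 0.05. At the 0.005 stated in the sample-size text it has 88.3%, and 98% would need 231 patients. That mismatch is a separate matter. The analysis text uses 0.05, so 0.05 is used below.

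**Model for period.** Let τ be the true evening-minus-morning difference in LDL-C reduction and π the period-2-minus-period-1 shift. The within-patient evening-minus-morning difference has mean τ + π in the morning-first sequence (n₁ completers) and τ − π in the evening-first sequence (n₂).

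- Bias of the plain paired mean: π(n₁ − n₂)/N.
- SD that the paired test estimates when n₁ ≈ n₂: √(13.80² + π²), which is 14.68 at π = 5 and 17.05 at π = 10.
- True standard error of the mean for a fixed split: still 1.10. Only the estimated standard error is inflated, which is why the test is conservative.
- Period-adjusted estimate: the average of the two sequence means, (τ + π + τ − π)/2 = τ. The shift cancels whatever the split.

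**Assumed inputs.** π = 5 or 10 mg/dL; completers 78/79 or 85/72. The document gives neither quantity.

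**Results at two-sided alpha 0.05, N = 157 (simulation)**

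| π (mg/dL) | Split | Bias (mg/dL) | Paired t: power | Paired t: type I error | Period-adjusted: power / type I error |
|---|---|---|---|---|---|
| 0 | 78/79 | 0 | 98% | 5% | 98% / 5% |
| 5 | 78/79 | about 0 | 97% | 3.7% | 98% / 5% |
| 10 | 78/79 | about 0 | 94% | 1.5% | 98% / 5% |
| 5 | 85/72 | 0.41 either way | 94% or 99% | about 5% | 98% / 5% |
| 10 | 85/72 | 0.83 either way | 80% or 99% | about 5% | 98% / 5% |

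Bias check: 10 × (85 − 72)/157 = 0.83, and 0.83/4.46 = 19% of the target. At π = 5, 0.41/4.46 = 9%. In the last two rows, the power depends on whether the bias works against or with the true effect. The near-nominal type I error in those rows arises because the inflated standard error offsets the bias. It does not show that the estimate is sound.

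**Worst case of the open list.** Treating morning and evening values as independent samples gives a standard error of √((31.49² + 30.35²)/157) = 3.49 instead of 1.10. The simulated chance of detecting 4.46 mg/dL is then about 2%.

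**The case against.** The strongest reply is that the listed tests are not wrong in themselves; it depends on how they are used.

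- A two-sample t or Mann-Whitney test on within-patient period differences, compared between sequences, is a standard period-adjusted crossover analysis, and both tests are on the list. This stands, although the article does not describe that use.
- Independent-sample tests are correct for the week-6 comparison, where the arms are different patients, and for the planned subgroups. This also stands.

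A reader might infer that power will collapse from 98% to about 2%. The document does not support that. The sample-size text uses a dependent t test with the morning-evening correlation, and the signed rank test is listed, so the natural reading is a paired comparison. A reader might also infer that binary endpoints will be tested wrongly, but the Endpoints section lists none. Nor is the paired test without period grossly invalid: with balanced sequences it errs on the cautious side.

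The pilot SD may already contain period variation if it was pooled over both sequences. In that case the plain paired test would not fall below its planned power, and the adjusted test would gain instead. At π = 10, for example, the within-sequence SD would be √(190.53 − 100) = 9.51. The argument for adjustment survives either way.

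Standardised fasting samples, a single analyser and free drug limit drift but do not exclude it.

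Finally, period terms might be left to an analysis plan. That would answer silence. Here the article names its methods, and the sizing test and the list contain no period-adjusted form.

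**Conclusion.** The point holds in a limited form. The article commits to a paired sizing test and a list of tests, none described so as to adjust the morning-evening contrast for period, and it includes two independent-group methods that cannot validly compare weeks 0, 6 and 12 within patients.

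The likely harm is moderate. For assumed shifts of 5 to 10 mg/dL it is a few points of power and a conservative test when sequences are balanced. At an assumed 85/72 split it is a bias of 9% to 19% of the target difference, with power as low as about 80% at the larger shift. All sizes rest on the pilot SDs and correlation, on the pilot SD of 13.80 being free of period variation, and on shifts and splits that the document does not give. The structural point rests on none of these: the period-adjusted analysis is unbiased by period at any split and gives up almost nothing when there is no period effect.

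**What to change.** Name one primary analysis of morning versus evening LDL-C: a linear mixed model with time of day, period, sequence and a random patient effect. With complete pairs, a two-sample t test on within-patient period differences (week 12 minus week 6) compared between sequences gives the same contrast, as half the difference between the sequence means. Mann-Whitney on those differences is the rank counterpart. Report the morning-evening difference with its 95% CI.

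Use the same approach for the other continuous endpoints. State that one-way ANOVA and Kruskal-Wallis will not be used for repeated measurements within patients. Keep independent-sample tests for the between-arm week-6 comparison and for subgroup comparisons.

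The cost is some wording, one model fit and one degree of freedom, with no new data. At N = 157 the adjusted test keeps 98% power at alpha 0.05. The article reports that recruitment is under way, so the change can still be written down before the analysis.

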### Safety of the trial

The study is limited only to patients with diagnosed hypercholesterolemia, in whom statin monotherapy does not allow one to reach the therapeutic goals. Moreover, all participants receive medications of all other groups recommended by the European Society of Cardiology guidelines accordingly to their comorbidities.

## Discussion

The RosEze trial is a phase IV, single-center, randomized, open-label, crossover study evaluating the effectiveness of combined therapy with rosuvastatin and ezetimibe for hypercholesterolemia depending on timing of the day of administration of the study treatment. This trial will reveal whether there is a significant difference in the effectiveness in reducing the concentration of cholesterol when the medications are taken in the morning compared with the evening time of the day. Considering that most medications are taken in the morning, it is possible that compliance with administration targets will improve if an effective dose can be taken in the morning instead of the evening.

### The study status

The study is currently recruiting participants. It was registered in the ClinicalTrials.gov database with identifier NCT02772640.

## Abbreviations

ALT: Alanine aminotransferase
Apo AI: Apolipoprotein AI
ApoB: Apolipoprotein B
AST: Aspartate aminotransferase
CAD: Coronary artery disease
CK: Creatine kinase
CVD: Cardiovascular disease
GGT: Gamma-glutamyl transferase
HbA1c: Hemoglobin A1c
HDL-C: High-density lipoprotein cholesterol
Hs-CRP: High-sensitivity C-reactive protein
LDL-C: Low-density lipoprotein cholesterol
